### Sample size

The sample size calculation was based on the demonstration of noninferiority of the watchful waiting strategy compared to the use of antibiotics for 7 days strategy. A sample size of 295 patients per group (total of 590 patients), with a one-sided t test for noninferiority (with a significance level of 0.05), has 80% power to reject the null hypothesis that the number of VFDs at 28 days in the Watchful Waiting Group is inferior to the number of VFDs at 28 days in the Antibiotic Treatment Group for 7 days by a margin of 20% and a coefficient of variation of 1.38,^(7)^ considering a potential loss to follow-up or dropouts of 10%.

The choice of the 20% noninferiority margin was motivated by what was considered acceptable by the Steering Committee from a clinical perspective. This 20% noninferiority margin translates into a 1.5 VFD difference at 28 days, considering the mean VFD of 7.69 days and the standard deviation (10.67) in patients with VAT from a prior publication.^(7)^

### Interim analysis

We plan to conduct interim analyses after the inclusion of 1/3 (196 subjects) and 2/3 (392 subjects) of the estimated sample, which will be performed by an independent Data and Safety Monitoring Board. The goal of this analysis is to stop the trial early for safety reasons if clearly superior outcomes are observed in the antibiotic treatment group regarding the primary outcome (VFDs), which will be determined using the Haybittle-Peto boundary^(28)^ (p < 0.001) in each interim analysis, without adjustments of the p value for group sequential analyses. There was no specific a priori planning to terminate the trial for futility or efficacy.

### Statistical analysis

The main analysis will follow the intent-to-treat framework, where the null hypothesis is that the number of VFDs up to 28 days in the Watchful Waiting Group is less than the number of VFDs in the Antibiotic Treatment Group for 7 days by a margin of 20%. If the upper bound of the 95% confidence interval for inferiority of the Watchful Waiting Group is < 20%, we will reject the null hypothesis of inferiority. To estimate the effect of treatment on the primary outcome, as well as in the interim analyses, an appropriate statistical model adjusted for stratification variables will be used for this type of outcome according to the variable behavior: either a generalized additive model for location scale and shape with zero-inflated beta distribution or nonparametric tests with the calculation of measures of effect and confidence intervals using resampling techniques (bootstrap) can be used. The effect size will be estimated according to the model best fitted to the data, with a 1-sided 95% confidence interval (95%CI) for noninferiority. If the noninferiority hypothesis is satisfied, superiority for the primary outcome will be tested considering a 95%CI using a hierarchical closed testing procedure. A primary sensitivity analysis of this noninferiority analysis will be a per-protocol analysis. Although per-protocol analyses are usually the primary analysis framework recommended for noninferiority trials, the intention-to-treat analysis framework may lead to more conservative estimates in antimicrobial trials.^(29)^ A p value of 0.05 will be considered to indicate statistical significance in the final analysis.

We also performed preplanned sensitivity analyses of the primary outcome, including only patients with microbiologically confirmed VAT, and we analyzed the randomization groups as an instrumental variable. Preplanned subgroup analyses will include the following: patients with or without a diagnosis of coronavirus disease 2019 (COVID-19) or other viral pneumonia, age ≤ 60 or > 60 years old, diagnosis of trauma on admission, acute brain injury, invasive mechanical ventilation duration of ≤ 5 or > 5 days at the time of randomization and effective vs. ineffective empirical antimicrobial treatment for isolated pathogens.

For the outcomes including VAP as a secondary outcome, we will perform sensitivity analyses based on the definition of VAP, including the more specific and more sensitive definition of VAP (including possible and probable cases of VAP). These definitions are presented in the Supplemental Material.

All secondary analyses will follow the usual superiority framework for analysis. Further details on the statistical model for the primary outcome, secondary outcomes, sensitivity and subgroup analyses, and data presentation will be described in detail in the statistical analysis plan to be published before database closure, in accordance with international recommendations for reporting randomized clinical trials.

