### Randomization, allocation concealment, and blinding

Patients will be randomized in a 1:1 ratio to each treatment arm (Watchful Waiting Group *versus* Antibiotic Treatment Group for 7 days). Randomization lists will be generated by an independent statistician using R software^(22)^ in random block sizes to preserve allocation concealment and will be stratified by center and by suspected diagnosis of viral pneumonia. Randomization will be performed using a central online randomization system (RedCap) that is available 24 hours a day.

This is an open-label trial in which both patients and investigators are not blinded to the interventions, given the nature of the trial and the need to follow local treatment regimens based on local microbiology. The adjudicators and trial statisticians will be blinded to the treatment assignment.

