### Data collection

Patient data will be collected through an online case report form (e-CRF) using REDCap,^(25,26)^ developed by the data management team of Hospital Sírio-Libanês. Access to the e-CRFs will be password-protected and supported by the trial data management team.

Demographic and baseline data, including the Simplified Acute Physiology Score (SAPS) 3, laboratory data, data on physiological variables, previous antibiotic use, and use of steroids upon randomization, among others, were collected for all participants. Daily data on antibiotic utilization, microbiological cultures, and ventilatory support were collected for up to 28 days. Additional information on the data collection is available in the Supplementary Material.

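### The primary model names only the two stratification variables for adjustment: valid, but it leaves unused the precision available from prognostic baseline data the trial already collects

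*Protocol article*

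**What the plan says.** The protocol article, Statistical analysis, fixes an adjustment set for the primary outcome and for the interim analyses: "an appropriate statistical model adjusted for stratification variables will be used for this type of outcome according to the variable behavior". The section on randomization identifies those variables; the lists "will be stratified by center and by suspected diagnosis of viral pneumonia". No further covariate is named for the primary model.

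The same article shows that other prognostic values are at hand:

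- Data collection lists "Demographic and baseline data, including the Simplified Acute Physiology Score (SAPS) 3, laboratory data, data on physiological variables, previous antibiotic use", among other items.
- Trial outcomes includes the change in SOFA from randomization to 7 days, so SOFA at randomization is needed.
- Statistical analysis plans subgroups by age, cut at 60 years, and by "invasive mechanical ventilation duration of ≤ 5 or > 5 days at the time of randomization".

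The article also leaves room for more: "Further details on the statistical model for the primary outcome, secondary outcomes, sensitivity and subgroup analyses, and data presentation will be described in detail" in a statistical analysis plan that is to be published before database closure and is not shown here.

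**The concern.** VFDs combine two things. Patients who die by day 28 score zero; the others score the time spent free of invasive ventilation. Baseline severity, organ dysfunction, age and time already ventilated plausibly predict both parts. Eligibility runs from 48 hours to under 21 days of ventilation, so patients enter at quite different points in their course, and neither stratification variable measures this directly.

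In a noninferiority trial, a wider interval makes it harder to show noninferiority when it is true. Variance that baseline data could explain but that stays in the residual widens the interval for no gain. More patients would be an expensive alternative: the Perspective section reports just over 180 included since June 2022 and warns that recruitment may slow.

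**Working it through.** **Inputs from the protocol article, Sample size.** The text gives "A sample size of 295 patients per group (total of 590 patients"), "with a one-sided t test for noninferiority (with a significance level of 0.05"), 80% power, a 20% margin, a coefficient of variation (CV) of 1.38 and 10% losses. It also gives a mean of 7.69 VFDs, an SD of 10.67 and a margin of 1.5 days. Note that 0.20 × 7.69 = 1.538.

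**Input not in the documents.** R², the share of VFD variance that the added covariates explain beyond center and suspected viral pneumonia, is assumed to be 0.05 to 0.20.

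**Step 1: reproduce the plan's figure.** On a log-normal ratio-of-means scale:

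- σ = √ln(1 + 1.38²) = 1.0326; margin = −ln 0.8 = 0.2231
- n = 2 × (1.645 + 0.842)² × 1.0326² / 0.2231² ≈ 265 per group
- 265 / 0.9 = 294.4, rounded up to 295

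This matches the stated 295 exactly. On the day scale the same formula with SD 10.67 gives 596 per group for a margin of 1.538 and 626 for a margin of 1.5, before losses. So power depends on the scale, and both are shown below.

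**Step 2: power with 265 evaluable per group, one-sided 0.05.** Power = Φ(margin / SE − 1.645), where SE = SD × √(2/265) × √(1 − R²).

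- Day scale, R² = 0: SE = 10.67 × √(2/265) = 0.927; 1.538 / 0.927 − 1.645 = 0.014; power 50.6%
- Log-ratio scale, R² = 0: SE = 1.0326 × √(2/265) = 0.0897; 0.2231 / 0.0897 − 1.645 = 0.84; power 80.0%

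| Assumed R² | Effective sample size, 1/(1 − R²) | Day scale, margin 1.538 | Day scale, margin 1.5 | Log-ratio scale |
|---|---|---|---|---|
| 0 | 1.00 | 50.6% | 48.9% | 80.0% |
| 0.05 | 1.05 | 52.3% | 50.6% | 81.8% |
| 0.10 | 1.11 | 54.1% | 52.4% | 83.6% |
| 0.20 | 1.25 | 58.3% | 56.5% | 87.2% |

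Applied to 590 patients, R² of 0.05, 0.10 and 0.20 is worth about 31, 66 and 148 extra patients (590 × [1/(1 − R²) − 1]).

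**Step 3: what adjustment cannot do.** To reach 80% on the day scale with 265 per group, R² would have to be 1 − 265/596 = 0.56 (margin 1.538) or 1 − 265/626 = 0.58 (margin 1.5). Both lie far above the assumed range.

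**Limits of the check.** The factor √(1 − R²) is a linear-model approximation, while the plan allows a zero-inflated beta model or nonparametric tests with bootstrap. The R² = 0 row uses the full SD. If center and viral pneumonia already explain some variance, every row starts somewhat higher.

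**The case against.** The strongest reply is that nothing here is wrong. Adjusting for the variables used to stratify randomization is standard and valid, and leaving out other covariates does not bias the comparison. That stands. The point concerns efficiency only.

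A reader might infer that the plan limits adjustment to the two variables. The text does not say so. It names them and leaves further model detail to a plan that is not shown, which may add covariates. Even so, the article does state an adjustment set, so this is a comment on a stated choice and not on a silence.

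A reader might also infer that the trial has only about 50% power. The documents state 80%, and that figure reproduces on the log-ratio scale. About 50% holds only on the day scale. That mismatch is a separate matter for the Sample size section, and the precision gain exists on both scales.

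Three further objections have weight:

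- **The R² is assumed.** It must be incremental to center, of which there may be up to 50, and viral pneumonia. The exclusions for instability, worsening gas exchange and poor short-term prognosis narrow the range of severity. The true gain could be at the low end or below it.
- **The gain is not entirely free.** In a zero-inflated beta model, covariate-conditional effects are not on the 20% or 1.5-day scale, so a standardisation step is needed. Under the nonparametric option, adding continuous covariates takes more thought.
- **Adjustment has a limited reach.** It accounts for chance imbalance in the covariates included, as far as they are modelled adequately. It does nothing about bias from open-label care.

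**Conclusion.** The point holds as an efficiency improvement. The named adjustment set is valid but forgoes precision that data already in the trial could supply. If the added covariates explain a further 5-20% of VFD variance, the effective sample size rises by about 5-25%. Power rises by about 2 to 8 percentage points on either scale: from 50.6% to 52-58% on the day scale, or from 80% to 82-87% on the log-ratio scale.

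This rests on an R² that the documents do not give, on 265 evaluable patients per group, and on a linear approximation to the planned model. The documents do not support reading it as an error in the analysis or as a cure for the scale mismatch in the sample size calculation.

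**What to change.** In the statistical analysis plan, before unblinding or database closure:

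- Add SAPS 3, SOFA at randomization, age and days of invasive ventilation at randomization to the primary model, as continuous terms, alongside center and suspected viral pneumonia.
- Report a standardised (marginal) difference or ratio of mean VFDs between arms, with a bootstrap or delta-method interval, and judge the 20% / 1.5-day margin on that scale.
- State a simple imputation rule for missing baseline values.
- If the covariates are deliberately left out, give the reason.

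The cost is wording, one standardisation step in the analysis code and the missing-value rule. No new data collection should be needed, since the values are already recorded or required by other planned analyses. The sample size scale should be reconciled separately, in the Sample size section.

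### The primary noninferiority method is chosen by fit to the trial data, and neither permitted method is tied to the mean-VFD scale on which the margin is set

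*Protocol article*

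**What the plan says.** In the protocol article, Statistical analysis, the primary outcome is to be analysed according to how the variable behaves, with "either a generalized additive model for location scale and shape with zero-inflated beta distribution or nonparametric tests" and bootstrap-based effect measures, adjusted for the stratification variables. The estimate is then settled by this sentence: "The effect size will be estimated according to the model best fitted to the data, with a 1-sided 95% confidence interval". The same choice of model is stated to apply at the interim analyses.

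The decision rule is relative: "If the upper bound of the 95% confidence interval for inferiority of the Watchful Waiting Group is < 20" per cent, inferiority is rejected. It does not say of which quantity the 20% is taken.

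The Sample size section does. It plans "with a one-sided t test for noninferiority (with a significance level of 0.05), has 80% power", "by a margin of 20% and a coefficient of variation of 1.38", and adds: "This 20% noninferiority margin translates into a 1.5 VFD difference at 28 days", derived from a mean of 7.69 and an SD of 10.67.

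The article defers further detail on the primary model to an analysis plan to be published before database closure. It also says that the trial statisticians are blinded to assignment.

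**The concern.** Two features combine. First, the article does more than leave the model open: it states a selection rule, fit to the trial's own data, for the only confirmatory noninferiority decision. Secondly, it does not say which quantity either method must deliver. A zero-inflated beta model yields a zero probability, a mean among nonzeros, and an overall mean built from both. A nonparametric analysis may report a mean difference, a median difference or a Hodges-Lehmann shift. The 20% (1.5-day) margin was set on the mean, and only a contrast of means can be judged against it.

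The distinction matters for this outcome because everyone who dies by day 28 scores zero (Trial outcomes). Harm may therefore appear mainly as more zeros, to which several of these measures barely respond. Goodness of fit cannot choose between them, because they are different estimands and not rival estimates of one.

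**Working it through.** **Inputs.** From Sample size: one-sided alpha 0.05, power 80%, 295 per group, margin 20% (0.20 × 7.69 = 1.538, stated as 1.5), SD 10.67, coefficient of variation 1.38, dropout 10%. Assumed: the control share with zero VFDs, which the article does not give; it was varied from 0.30 to 0.64. The stated moments cap it. P(VFD > 0) is at least mean²/(mean² + SD²) = 59.14/(59.14 + 113.85) = 0.342, so the zero share cannot exceed 0.658.

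**Step 1: the plan's own figure.** On a lognormal ratio-of-means scale, the margin is −ln 0.8 = 0.2231 and the SD is √ln(1 + 1.38²) = 1.0326. Then n = 2(1.645 + 0.842)² × 1.0326²/0.2231² = 265 per group, and 265/0.90 = 294.4, which rounds up to 295. The figure is reproduced. A difference in means does not reproduce it: 596 per group (margin 1.538) or 626 (margin 1.5) before dropout. In either case the inputs are a mean, its SD and its coefficient of variation; no median or rank shift enters.

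**Step 2: one case by hand.** Take zero shares of 0.55 (control) and 0.64 (watchful waiting), with the same nonzero distribution in both arms, of mean 7.69/0.45 = 17.1.

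- Overall mean: (0.36 × 17.1)/(0.45 × 17.1) = 0.80, a loss exactly at the margin. The beta model's overall mean, (1 − zero probability) × nonzero mean, gives the same.
- Median: both zero shares exceed 0.5, so both medians are 0. The difference is 0 and a relative loss is undefined.
- Hodges-Lehmann shift: P(watchful waiting lower) = 0.45 × 0.64 + ½ × 0.36 × 0.45 = 0.369, and P(both zero) = 0.55 × 0.64 = 0.352. The median pairwise difference falls within the ties, so the shift is 0.
- Nonzero part alone: 17.1/17.1, a 0% loss. The odds ratio for zero is (0.64/0.36)/(0.55/0.45) = 1.45.

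**Step 3: simulation.** 265 evaluable patients per group; VFDs zero-inflated beta on 0 to 28, matched to mean 7.69 and SD 10.67; true mean loss exactly 20%. There were 500 trials per cell for zero shares up to 0.45 and 1,000 above. Bounds were one-sided 95%: bootstrap, or Wilcoxon-type for Hodges-Lehmann. Day-scale measures were read against 1.5 and ratios against 0.8. The nonzero part was approximated by a bootstrap mean ratio; the full beta model was not fitted.

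Percentage of trials declaring noninferiority, loss entirely through extra zeros:

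| Zero share, control → watchful waiting | Mean ratio | Mean difference | Median difference | Hodges-Lehmann | Nonzero mean ratio |
|---|---|---|---|---|---|
| 0.30 → 0.44 | 4.8 | 3.8 | 89.8 | 100 | 67.4 |
| 0.40 → 0.52 | 2.8 | 2.4 | 78.2 | 100 | 71.0 |
| 0.45 → 0.56 | 5.6 | 4.6 | 77.2 | 100 | 77.2 |
| 0.50 → 0.60 | 6.1 | 6.0 | 82.2 | 100 | 82.3 |
| 0.55 → 0.64 | 5.7 | 5.4 | 87.6 | 100 | 89.9 |
| 0.60 → 0.68 | 4.8 | 5.3 | 98.0 | 100 | 97.8 |
| 0.64 → 0.71 | 5.2 | 4.3 | 99.8 | 100 | 100 |

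When the loss lies wholly in the nonzero part, the nonzero mean ratio behaves (4.6 to 9.4%), the mean ratio gives 4.4 to 8.4% and the mean difference 4.2 to 7.4%. With a mixed loss, the nonzero mean ratio gives 31 to 88%. The median difference stays above 80% in both of these settings, and Hodges-Lehmann at 100%.

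A separate run with VFDs in whole days, a 1.54-day margin and zero shares of 0.45 to 0.58 gave 3 to 5% for the mean difference, 60 to 91% for the median difference and 100% for Hodges-Lehmann. The low end for the median thus depends somewhat on how the outcome is modelled.

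**Not tested.** These runs fix the effect measure in advance. Selecting the method by best fit was not simulated, so no figure here measures error inflation from that selection.

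**The case against.** The article names neither a median difference nor a Hodges-Lehmann shift, and does not propose testing one component of the beta model alone. Because the margin is set on the mean, a bootstrap of the mean is a natural reading, and under it the error stays near 5%. The decision rule is also relative, so comparing a median or rank shift with 1.5 days is not what it literally prescribes. All of this stands.

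A reader might go further and infer three things that the document does not support.

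- That the two methods necessarily estimate different quantities, or that the nonparametric option by its nature declares noninferiority almost always. Both can deliver the overall arm mean; the high rates belong to particular measures that the text leaves open.
- That a nonparametric test contradicts the required adjustment for stratification variables. Stratified rank tests, such as van Elteren's, exist.
- That a later analysis plan cannot cure the problem. A plan published before database closure, with statisticians blinded to assignment, could name the estimand and settle the model before unblinding.

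What survives is the stated rule itself. A plan that merely elaborates it carries it forward; one that fixes a single estimand has to override it. Blinding limits deliberate selection but does not supply an estimand. Publication before database closure also does not guarantee that the choice precedes the interim looks at 196 and 392 patients, and more than 180 were already enrolled when the article was drafted.

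**Conclusion.** The concern holds in a limited form. The article lets fit to the trial data choose the primary noninferiority method and ties neither option to the mean-VFD scale of the margin. Reported as a contrast of overall means, either option can hold false noninferiority near the nominal 5% (about 2 to 8%). Read through a median difference, a Hodges-Lehmann shift or the nonzero part alone, the rate is about 67 to 100% when the loss arises through extra zeros, with 60% as the lowest median result in the whole-day run.

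These rates rest on an assumed zero share, a zero-inflated beta outcome and effect measures that the text permits without naming. They show that the choice of measure decides the type I error; they do not show that the trial will use a failing one. I would class this as a should-fix with moderate confidence.

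**What to change.** State now that the primary estimand is the contrast in mean VFDs at 28 days between arms, as a ratio or a difference, and express the margin on that same scale. Prespecify one model adjusted for the stratification variables, standardise its predictions over all randomised patients to arm means, and compare a one-sided 95% bootstrap bound with the margin. Make the other method a sensitivity analysis that cannot replace the primary. Replace the best-fit sentence accordingly. At the least, require any model choice to be made on blinded pooled data before unblinding, and to change only how the mean contrast is estimated.

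The cost is a few sentences in the protocol and analysis plan and a short standardisation and bootstrap routine; no new data are needed. Naming the contrast will, however, draw attention to power. With 265 evaluable per group and SD 10.67, the standard error of a mean difference is 10.67 × √(2/265) = 0.927. Assuming no true difference, power is Φ(1.5/0.927 − 1.645) = 49%, or 51% with a margin of 1.538. That is a separate matter, but the choice between ratio and difference should be made with it in view.

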**Inclusion criteria**
1. Adult patients (age ≥ 18 years old)
2. Admitted to ICU
3. Invasive mechanical ventilation for at least 48 hours
4. Presence of clinical criteria for VAP, defined as: a. Temperature > 38°C or < 36°C **OR** leucocyte > 12,000/mL or < 4,000/mL or > 10% immature forms **AND** b. New onset of purulent tracheal secretions **OR** change in secretion characteristics **OR** increase in secretions volume **OR** increased suctioning requirements
5. Lower respiratory tract microbiological sample under analysis or collection on the day of trial triage
6. Chest imaging (chest X-ray or computed tomography) on the day of trial triage

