**Exclusion criteria**
1. Pregnancy or active lactation
2. Current use or indication of use of systemic antibiotics for any reasons
3. Hemodynamic instability, defined as new-onset hypotension unresponsive to fluid boluses or increase in vasopressor dose > 0.1mcg/kg/minute of norepinephrine or equivalent in the previous 6 hours
4. Worsening gas exchange, defined as an increase in the oxygen-inspired fraction ≥ 20% or an increase in PEEP ≥ 3cmH_2_O after a period of stability of ≥ 2 days
5. Prolonged mechanical ventilation, defined as an invasive mechanical ventilation duration ≥ 21 days
6. A new pulmonary opacity on chest image suggestive of new infectious infiltrates
7. Previous pulmonary disease that hampers the radiographic interpretation for VAP diagnosis
8. Previous diagnosis of VAP during hospitalization
9. Neutropenia (absolute neutrophil count < 1,000/mL)
10. Severe known immunosuppression
11. Tracheostomy on the day of trial triage
12. Prior inclusion in the trial in the last 30 days
13. Expected withholding or withdrawing of life support within 7 days
14. Patients unlikely to survive > 48 hours
15. Consent refusal to participate in the trial

ICU - intensive care unit; VAP - ventilator-associated pneumonia; PEEP - positive end-expiratory pressure.

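### Age and prior ventilation time appear in the subgroup plan only as two-group splits; if the treatment effect changes gradually with either, testing on the splits discards roughly a third to a half of the information

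*Protocol article*

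**What the plan says.** The protocol article, under Statistical analysis, names six preplanned subgroup analyses. The list includes "age ≤ 60 or > 60 years old, diagnosis of trauma on admission, acute brain injury, invasive mechanical ventilation duration of ≤ 5 or >", so that two of the six cut a continuous baseline measure: age, and ventilation time, whose item reads in full "invasive mechanical ventilation duration of ≤ 5 or > 5 days at the time of randomization". No continuous analysis of either is mentioned.

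The same section defers the modelling: "sensitivity and subgroup analyses, and data presentation will be described in detail in the statistical analysis plan", which is to be published before the database is closed.

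Eligibility leaves both measures a wide range. Table 1 admits adults from 18 years with no upper age limit. It requires "Invasive mechanical ventilation for at least 48 hours" and excludes "Prolonged mechanical ventilation, defined as an invasive mechanical ventilation duration ≥ 21 days". Ventilation time at entry can therefore run from 2 days to just under 21. The trial must hold both values to check eligibility and assign the subgroups, and Data collection lists demographic and baseline data for all participants.

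**The concern.** A cut at 5 days treats a patient on day 6 like one on day 20 and separates day 5 from day 6. A cut at 60 years does the same for age. If the effect of withholding antibiotics rises or falls gradually along these scales, the variation within each half is lost to the comparison of the two halves.

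Readers are likely to ask whether watchful waiting performs similarly in older patients and at different points in the course of ventilation. The trial is sized for the overall comparison, so any interaction test will be weak. A less efficient test makes it more likely that real heterogeneity goes unseen, and it ties the answer to one cut-point.

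**Working it through.** **The plan's own figure.** The article states no power or information figure for subgroups. Its only related figure is the sample size, which reproduces on the log-ratio scale:
- SD = √ln(1 + 1.38²) = 1.033; margin = −ln 0.80 = 0.223; one-sided 5%, 80% power.
- n = 2 × (1.645 + 0.842)² × 1.033² / 0.223² ≈ 265 per group.
- 265 / 0.9 gives 295 per group, 590 in total.

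**Inputs for the check.** From Sample size: N = 590, SD of ventilator-free days 10.67, 1:1 allocation. Assumed: two-sided 5%, and a treatment effect that changes linearly with the modifier, by g days per SD. The distributions of age and ventilation time are also assumed.

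**Information kept by a split (normal modifier).** Let p be the share on one side of the cut c, and φ the normal density.
- Continuous term: SE = 2 × SD / √N.
- Split: expected difference in treatment effect = g × φ(c) / [p(1 − p)]; SE = 2 × SD / √[N p(1 − p)].
- Relative efficiency, the squared ratio of the two z-values: φ(c)² / [p(1 − p)].

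| Split | φ(c) | p(1 − p) | Kept | Lost |
|---|---|---|---|---|
| 50/50 | 0.399 | 0.2500 | 0.64 | 36% |
| 60/40 | 0.386 | 0.2400 | 0.62 | 38% |
| 70/30 | 0.348 | 0.2100 | 0.58 | 42% |
| 74/26 | 0.324 | 0.1924 | 0.55 | 45% |
| 75/25 | 0.318 | 0.1875 | 0.54 | 46% |

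**Other assumed distributions.** The information kept is the squared correlation between the modifier and its split indicator.
- Age cut at 60, normal, mean 50–65, SD 15–20: 36–46% lost; truncated to 18–95 years, 32–43%. With mean 45 the loss is 40–56%.
- Age uniform on 18–90: p = 30/72, kept = 3p(1 − p) = 0.73, so 27% lost.
- Ventilation time on 2–21 days, cut at 5, shifted exponential (scale 2–12 days): 35–54% lost.
- Lognormal, median 4–5 days: 37–49% lost; median 6–8 days: 52–76%.
- Uniform on 2–21 days: p = 16/19, kept = 0.40, so 60% lost.

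**What this means for power.** SE of the continuous interaction = 2 × 10.67 / √590 = 0.88 days per SD. Power = Φ(g/SE × √kept − 1.96) + Φ(−g/SE × √kept − 1.96), with kept = 1 for the continuous term.

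| g (days per SD) | Continuous | 50/50 split | 75/25 split |
|---|---|---|---|
| 0.50 | 8.8% | 7.4% | 7.0% |
| 0.75 | 13.7% | 10.5% | 9.6% |
| 1.72 | 50% | 35% | 30% |
| 2.46 | 80% | 61% | 54% |

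N = 590 ignores the 10% dropout allowance. With 530 evaluable patients the SE becomes 0.93, and 50% power needs 1.96 × 0.927 = 1.82 days per SD.

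**Check on a realistic outcome.** Simulations of zero-heavy ventilator-free days (mean about 7.7, SD about 10) under assumed modifier distributions gave power of 67% continuous versus 49% split for age, and 56% versus 31% for a right-skewed ventilation time. Converting power to z (1.96 + Φ⁻¹(power)) gives 1 − (1.935/2.400)² = 35% lost for age and 1 − (1.464/2.111)² = 52% for ventilation time. Both agree with the ranges above.

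**The case against.** The strongest reply is that the article only lists subgroups. It states no interaction test and leaves the model to an analysis plan that may already contain a continuous interaction. That stands: a reader might infer that the trial will test effect modification only through the splits, and the article does not establish this. What remains is that these cuts are the only form in which the article specifies the two modifiers.

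Second, the loss depends on a gradual effect. If the modification were a step exactly at 60 years or 5 days, the split would be the better test. This also stands, although the article gives no reason to expect such a step. That it gives no reason for the cuts is not itself a fault, since a condensed article commonly leaves such reasons to the full protocol.

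Third, the gain is modest where interactions are modest. At 0.75 days per SD, power is 13.7% against 10.5%, so both tests are nearly uninformative. Reaching 50% power with the continuous term needs about 1.7 days per SD, which is more than the trial's whole 1.5-day margin. This limits the practical importance of the point but does not remove it.

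**Conclusion.** The point holds in a limited form. The article specifies two continuous modifiers only as two-group splits. For a linear interaction, testing on those splits loses about 36–45% of the information with a roughly normal modifier split between 50/50 and about 75/25. With a bounded, right-skewed ventilation time the loss is about 35% to over 50%, and it could be higher still if most patients are past day 5 at entry.

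A reader might take a single percentage as a fact about this trial. The documents do not support that: they give no distribution for either modifier, and a flat age distribution would lose only about 27%.

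Nor does the point reach the main result. The noninferiority comparison, its decision rule and the sample size do not use these splits. It is a low-cost improvement to secondary analyses and does not affect the trial's validity.

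**What to change.** In the analysis plan, before database closure, prespecify treatment-by-age and treatment-by-days-ventilated-at-randomisation interactions within the primary-outcome model, with both modifiers continuous. Use the linear term as the test and show a restricted cubic spline of the treatment effect for display. Keep the 60-year and 5-day groups as descriptive rows in the forest plot, which preserves what the article announced. If the plan already does this, nothing needs to change.

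The cost is one or two sentences, with no new data and no extra patients. The small downside is that a linear test is less efficient if the true modification is a step at the cut. The spline and the retained subgroup rows would let readers see that.
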